#### Covariates

Potentially important covariates (prognostic factors) to include in the analysis are:

Age.Gender.Anxiety/depression.Number of previous surgeries (TMJ-related).Onset of disease.Underlying disease.Use of pain medications.Smoking.Type of implant.Geographic region.Baseline scores.Unilateral/bilateral joint replacement.

#### Radiological parameters

All images collected according to the local standard of care will be evaluated according to the following postoperative parameters:

Displacement of the ramus component.Fracture of the ramus component.Screw loosening.Resorption/osteolysis of the surrounding bone.Status of bone grafts if used (displaced/resorbed/healed).Presence of ectopic bone.

All images collected per standard of care may be used for further analysis, either on-site or by a central reader. Preoperative image analysis will depend on registry findings.

### Statistical analysis

Since the objectives of this registry are descriptive and exploratory in nature, no formal hypothesis testing is planned, and all analyses will be exploratory. The planned sample size of 200 patients is based on the estimated number of eligible participants expected to be enrolled during the 2-year recruitment period. Eligible patients who refuse TMJ replacement will be included in the study but excluded from sample size calculations. Depending on the volume and quality of the data collected during the first 2 years, the registry may remain open thereafter, with patient FU of up to 5 years.

A detailed statistical analysis plan (SAP) will be finalised before the final analysis (ie, the analysis from which the results will be summarised in the final registry report). As the primary aim of the current registry is descriptive, patient characteristics, clinical data and outcomes recorded at standard-of-care scheduled FU assessments will be presented using descriptive summary statistics. Categorical variables will be summarised using frequency and percentage for each category. Continuous variables will be summarised using the mean, SD, median, IQR and minimum and maximum values. Analyses will also be stratified by clinically relevant categories, including treatment patterns.

Longitudinal clinical, functional and PRO data may be analysed using mixed-effects models for repeated measures, allowing inclusion of all available data and minimising the impact of missing data. Time-to-event analyses are planned, with survival status recorded at each scheduled FU. Kaplan-Meier methods will estimate survival probabilities, and multivariable Cox proportional hazards models will be used where event numbers permit.

Centre effects and geographic variability will be addressed using multilevel (hierarchical) models with patients nested within regions to account for clustering and differences in practice patterns. For time-to-event outcomes, region (or treating centre) will additionally be included as a covariate in Cox regression models when sample sizes permit. The AEs will be summarised at both patient and event levels, with rates calculated using the total population as the denominator, regardless of dropouts, with 95% CIs provided.

As the registry is embedded within routine clinical care, assessments are performed according to each centre’s standard practice. To support consistent data capture, all site investigators and study coordinators will receive structured training prior to enrolment, covering registry procedures, eligibility criteria, use of the eCRF and adherence to Good Clinical Practice principles. Data completeness is monitored centrally through the eCRF system, with sites supported in resolving missing or inconsistent entries.

For specific research questions, suitable patient subgroups will be identified and included. Criteria for inclusion, handling of missing data and protocol violations will be defined in the SAP before analysis.

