Although it is one of the most frequently used joints in the body, the TMJ is replaced with alloplastic implants much less frequently than joints such as the hip or knee.^23^ This may be partly attributable to the poor performance of early devices, which were associated with high failure rates, frequent revisions, suboptimal trial design and limited outcome monitoring.^7 20^ In addition, the readability, reliability, content and overall quality of online information on TMDs vary widely, which may further contribute to patients’ reluctance to pursue surgical treatment.^24^ Advances in personalised implant design, materials and biomechanics have made modern TMJ replacements safer and more effective.^1920 25^,^27^ As a result, the use of this treatment has increased, with procedure numbers rising and further growth expected in the coming years.^21^

Despite these advances, high-quality clinical data remain limited.^23 28^ Most published studies—excluding case reports—consist of retrospective series from a few centres, often with limited sample size and a potential risk of conflict of interest.^2229^,^31^ Although reported outcomes are generally positive, key questions regarding patient selection, optimal timing of intervention and whether early replacement is beneficial or should be reserved for specific patient subgroups remain unanswered. The UK has established a national TMJ replacement database,^32^ developed under the auspices of the British Association of TMJ Surgeons, to collect longitudinal outcome data within the UK. This database enables surgeons to compare outcomes with peers and share long-term results. However, no global registry currently exists. This highlights the need for international, multicentre studies to better define indications, outcomes, costs, complications and long-term effects of alloplastic TMJ replacement.

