#### Adverse events (AEs)

Since this is an observational registry, only anticipated condition-related, treatment-related or implant-related AEs will be documented from the time of consent onwards. These include fixation failure (implant loosening, breakage or instability), dehiscence of incision, wound infections, neurological-related (facial nerve damage, Frey’s syndrome, sensory disturbances or altered hearing), bleeding, haematoma, swelling, injury to adjacent structures, ankylosis, malocclusion, sensitivity to material, heterotopic ossification, disarticulation, contralateral joint dysfunction, condylar resorption, graft loss, revision surgery and any other AEs that may affect the outcome of the registry.

These events are considered events of scientific interest, that is, events that can clearly be connected to the treatment(s) or the medical condition under investigation and will not require immediate reporting to the local EC/IRB unless they occur at a higher frequency and/or severity than that cited in the literature.

This registry can be considered a minimal-risk study, given that participation poses a very low risk compared with the standard-of-care (routine) procedures.

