#### Survival

Patient’s survival will be documented at each FU visit. If a visit is missed, survival will be confirmed by phone call.

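### The planned survival curves follow the patient's survival, while device failure and revision are left to crude rates that take no account of loss to follow-up

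*Protocol article*

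**What the plan says.** All references are to the protocol article.

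- **Statistical analysis.** "Time-to-event analyses are planned, with survival status recorded at each scheduled FU". The next sentence reads "Kaplan-Meier methods will estimate survival probabilities, and multivariable Cox proportional hazards models will be used where event numbers permit". A later sentence refers to such outcomes in the plural but names none: "For time-to-event outcomes, region (or treating centre) will additionally be included as a covariate in Cox regression models when sample sizes permit".
- **Survival (under Outcome measures).** The subject is the patient: "survival will be documented at each FU visit", and "If a visit is missed, survival will be confirmed by phone call". The Survival row of Table 2 is ticked at every postoperative visit.
- **Adverse events.** Device failure is listed here, as "fixation failure (implant loosening, breakage or instability" and, at the end of the list, "graft loss, revision surgery and any other AEs that may affect the outcome of the registry". The Statistical analysis section summarises adverse events per patient and per event, as rates with 95% CIs. The denominator is everyone, including those who left early.
- **Radiological parameters.** Ramus-component displacement and fracture, screw loosening and osteolysis are read from routine images. Table 2 marks these at 10 days, 12 months and 24 months.
- **Premature termination of participation.** Death appears among the reasons for early termination, and the data of such participants are to be censored at that point.
- **Strengths and limitations.** Missing data over the 60-month follow-up are expected.

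**The concern.** Two methods are assigned to two kinds of event, and the assignment looks the wrong way round. Kaplan-Meier and Cox allow for unequal follow-up, but the only status variable attached to them is the patient's survival. Loosening, breakage and revision occur over years and are exposed to loss to follow-up, yet they get a proportion that counts a patient lost at 6 months as a patient observed free of failure to 60 months.

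The Introduction names complications and long-term effects among the gaps in knowledge, and the Discussion promises comparison of complication rates and research on long-term outcomes. If the analysis is run as written, the survival curves do not bear on how the devices last. The figure that does bear on it is biased low, by an amount that depends on how many patients each centre loses. Centres with poorer retention would tend to show lower failure rates.

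**Working it through.** **1. What the survival variable is.** The Statistical analysis section takes survival status at scheduled visits as the input. The Survival section and the Table 2 row give the only meaning: the patient is alive or not, checked by telephone if a visit is missed. A search of the article for time to revision, removal, exchange or fixation failure finds none. The section on what the SAP will define lists inclusion criteria, missing data and protocol violations; event definitions are not among them.

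**2. Death as event or as censoring.** Premature termination lists death and censors the data of those who terminate. If death is the event in the Kaplan-Meier analysis, a literal reading of that rule censors the event itself. If death is only a reason for censoring, the survival analysis has no event defined. One of the two passages needs a qualifier.

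**3. Size of the bias in the crude rate.** The article gives no failure or loss rate, so there is no figure to reproduce and all rates here are assumptions. Let p be the true 5-year failure and d the 5-year loss to follow-up, both at constant hazard and independent of each other:

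- λ = −ln(1 − p)/5 and μ = −ln(1 − d)/5
- crude proportion = λ/(λ + μ) × [1 − exp(−5(λ + μ))], where the bracket equals 1 − (1 − p)(1 − d)

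For p = 0.10 and d = 0.20: λ = 0.0211, μ = 0.0446, λ/(λ + μ) = 0.321, bracket = 1 − 0.90 × 0.80 = 0.28, crude = 0.321 × 0.28 = 0.090.

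For p = 0.10 and d = 0.40: μ = 0.1022, λ/(λ + μ) = 0.171, bracket = 1 − 0.90 × 0.60 = 0.46, crude = 0.171 × 0.46 = 0.079.

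| True 5-year failure | Crude, 20% lost | Crude, 40% lost |
|---|---|---|
| 5% | 4.5% | 3.9% |
| 10% | 9.0% | 7.9% |
| 15% | 13.5% | 11.8% |

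The crude figure is about 0.90 of the truth with 20% lost and about 0.79 with 40% lost. Reporting before all patients reach 60 months would lower it further in the same way.

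**4. Size against sampling error.** With 200 patients fully followed, the 95% CI half-width is 1.96 × √(p(1 − p)/200): 3.0, 4.2 and 5.0 percentage points at p = 5%, 10% and 15%. At 10% the bias is 1.0 to 2.1 points against a half-width of 4.2. It is smaller than the random error, but it always acts in one direction and a larger registry would not remove it.

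**5. Events available.** Deaths in 200 patients over 5 years at annual mortality m are 200 × (1 − exp(−5m)): about 2, 5, 10 and 19 for m = 0.2%, 0.5%, 1% and 2%. Device failure of 5%, 10% or 15% by 5 years gives 200 × p = 10, 20 or 30 events.

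**6. Unit and clock.** Treatment details allow bilateral replacement and a later contralateral replacement, while Table 2 counts all follow-up from the treatment day. A single clock per patient does not give the time at risk of a second joint implanted later.

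**The case against.** The strongest reply is that a journal article condenses the protocol, and that the choice of events, unit and competing risks belongs to a SAP that is not shown and is not yet final. That would be decisive had the article been silent. It is not: it describes one survival status, the patient's, and sets a separate rule for the events that include device failure, one that disregards dropout. A SAP could still add the endpoint, which bears on severity.

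Several further points against a stronger reading stand.

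- A reader might infer that death is the sole endpoint and that the registry cannot say how long implants last. The article never equates the event with death, its wording on time-to-event outcomes is plural, and fixation failure, revision and radiological component failure are all collected. The limit lies in the analyses as written.
- A reader might infer that the registry was set up because of device failure. The phrase "high failure rates, frequent revisions, suboptimal trial design and limited outcome monitoring" describes early devices and explains low uptake; the same paragraph calls modern devices safer. The Objectives do not name implant longevity; their examples of favourable outcome are pain, range of motion, occlusion and quality of life.
- A reader might expect an overfitted Cox model from the small number of deaths and the 12 listed covariates. Cox is conditional on event numbers, and the covariates are described only as potentially important.
- Adverse events are reported as rates with 95% CIs, so device failure is not left to bare counts.
- The adverse-event form is not shown, so nothing establishes that it lacks the date or side of an event.

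**Conclusion.** The point holds in a limited form. As written, patient survival is the only status linked to the censoring-aware methods, and device failure goes to a rate that disregards dropout. That rate understates 5-year failure by about a tenth with 20% loss and about a fifth with 40% loss. These figures assume constant hazards and loss unrelated to failure; if patients whose device is failing are lost more often, or less often, the size changes. The treatment of death is inconsistent between Premature termination and Statistical analysis, whichever endpoint was meant.

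The document does not support calling this a fatal gap: the registry is exploratory, tests no hypothesis, collects the relevant events and has its SAP still open. It is a should-fix.

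**What to change.** In Statistical analysis:

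- Name time from implantation of a joint to first revision, removal or exchange as a time-to-event outcome, with time to first fixation failure as secondary.
- Estimate it by Kaplan-Meier with death censored, or by cumulative incidence with death as a competing event, and state which. Give 1-, 2- and 5-year estimates with 95% CIs.
- Start the clock at each joint's own operation and allow for two joints in one patient, for example with a cluster-robust variance.
- Keep Cox only where event numbers permit, as now. The crude adverse-event rates may stay as a description of documented events, labelled as such.

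Reconcile Premature termination with Statistical analysis, saying for each outcome whether death is an event, a competing event or a censoring reason.

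Confirm that the event date and side are captured. Unscheduled visits are not documented, and the last two scheduled visits are 60 − 24 = 36 months apart, so without a date a late revision could be placed only within that interval.

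The cost is wording, a little extra analysis and at most two form fields if they are not already there. No visits or patients are added. The fields are best checked now, because dates are harder to recover later.

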## Methods and analysis

### Study design and setting

This is a prospective, multicentre observational cohort study serving as a registry of patients with severe TMD from any cause, either congenital or acquired, requiring alloplastic total TMJ replacement. Table 1 summarises the sites that are currently included in the study.

**Table 1 T1:** Details of participating sites

Participating site	Country	Region
Oral Rehabilitation Centre, Bangalore	India	Asia
University Hospital Basel, Basel	Switzerland	Europe
Clinic for Maxillofacial Surgery, University of Belgrade, Belgrade	Serbia	Europe
Rigshospitalet, Copenhagen	Denmark	Europe
King Edward VIII Hospital, Durban	South Africa	Africa
Falu Hospital, Falun	Sweden	Europe
University Hospital Leipzig, Leipzig	Germany	Europe
Skåne University Hospital, Lund	Sweden	Europe
12 de Octubre University Hospital, Madrid	Spain	Europe
Medizinische Hochschule Hannover, Hannover	Germany	Europe
Pirogov National Medical and Surgical Center (NMSC), Moscow	Russia	Europe
Ludwig Maximilian University Hospital, Munich	Germany	Europe
Wojewódzki Specjalistyczny Szpital Dziecięcy, Olsztyn	Poland	Europe
Erasmus University Medical Center, Rotterdam	The Netherlands	Europe
Karolinska University Hospital, Stockholm	Sweden	Europe
A Beneficência Portuguesa de São Paulo, São Paulo	Brazil	South America
Uppsala University Hospital, Upphsala	Sweden	Europe
Universitätsmedizin Mainz, Mainz	Germany	Europe

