### Objectives

The study seeks to broaden understanding of TMDs, treatment patterns and patient outcomes, with a focus on clinical indications, regional variations and patient-reported, clinical and functional outcomes in patients undergoing alloplastic TMJ replacement. Additionally, the study aims to identify predictive factors for favourable outcomes (such as pain reduction, range of motion, occlusal status and QoL) and understand why some patients refuse TMJ replacement.

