### Study procedures

In this study, patients will receive treatment based on the local standard of care, with all intervention and postoperative care performed according to the standard procedures at participating sites, as determined by the treating surgeon. The study protocol will not influence clinical decision-making, materials or surgical/imaging techniques, except for the collection of standardised data in a customised database.

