### Current study status

To date, 18 ethically approved centres, the majority of which are European, are participating in this study (table 1). The first patient was enrolled in June 2021. The enrolment start date for each site is provided in the online supplemental table.

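### The multilevel model is meant to handle centre effects but groups patients only by region, so clustering among the 15 European centres is not modelled

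*Protocol article*

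**What the plan says.** The Statistical analysis section of the protocol article states the aim as "Centre effects and geographic variability will be addressed using multilevel (hierarchical) models" and then fixes the structure as "multilevel (hierarchical) models with patients nested within regions to account for clustering and differences in practice patterns". The next sentence, on time-to-event outcomes, offers region, or in brackets the treating centre, as a Cox covariate if sample sizes allow. Region and centre are thus used as different terms, and centre is not a level of the multilevel model.

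Table 1 (Study design and setting) assigns each site to a region. Asia is represented only by "Oral Rehabilitation Centre, Bangalore", Africa only by "King Edward VIII Hospital, Durban" and South America only by the São Paulo site. Current study status describes "18 ethically approved centres, the majority of which are European".

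Study procedures places the variation in practice at site level: "all intervention and postoperative care performed according to the standard procedures at participating sites, as determined by the treating surgeon". The text on training that follows the analysis plan says the same of assessments, and both the limitations list and the Discussion name differences between centres as a weakness. The Objectives include a study "with a focus on clinical indications, regional variations and patient-reported, clinical and functional outcomes" and the search for predictors of good outcomes. Type of implant is among the listed covariates.

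**The concern.** A random effect absorbs clustering only at the level where it is placed. The protocol expects practice to differ by centre, yet under the stated model patients from 15 hospitals in nine European countries share one region effect and are otherwise treated as independent. Outside Europe each region is a single hospital, so a regional result there is that hospital's result. The region variance itself would be estimated from four units.

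Two stated aims are exposed. Intervals for predictors tied to centre practice would look more precise than they are. Regional variation could not be told apart from variation between individual hospitals.

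**Working it through.** The protocol has no figure to reproduce: the sample size of 200 comes from expected enrolment, not from a power or precision formula. The check therefore has three steps.

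**1. Grouping structure.** Table 1 has 18 rows: Europe 15, Asia 1, Africa 1, South America 1. Europe holds 15/18 = 83% of sites. In three of the four groups, region and centre are the same unit.

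**2. Design effect for a predictor that is constant within centre.** Inputs are 200 patients (Statistical analysis) and 18 centres (Table 1). An even split is assumed, so m = 200/18 = 11.1. The ICC is not given, so a range is assumed. The design effect is DE = 1 + (m − 1) × ICC. If clustering is ignored, standard errors are too small by a factor √DE, and coverage of a nominal 95% interval is 2Φ(1.96/√DE) − 1.

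| Centre ICC | DE | √DE | Coverage | 200/DE |
|---|---|---|---|---|
| 0.02 | 1.20 | 1.10 | 92.6% | 166 |
| 0.05 | 1.51 | 1.23 | 89.0% | 133 |
| 0.10 | 2.01 | 1.42 | 83.3% | 99 |
| 0.15 | 2.52 | 1.59 | 78.3% | 79 |

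**3. Simulation of the region model itself.** The formula ignores clustering altogether, whereas the plan does fit a region effect, so the fitted model was simulated.

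- Patients and centres: 200 patients in 18 centres (16 of 11 and 2 of 12), with regions split 15/1/1/1.
- Outcome: one continuous outcome per patient with total variance 1, centre effects with variance equal to the ICC, and no true region effect.
- Predictor: binary with no true effect. Nine randomly chosen centres have the low probability and nine the high one.
- Fit: REML random intercept by region or by centre, with an interval of estimate ± 1.96 SE.
- Runs: 2,000 per cell, giving a Monte Carlo standard error of about 0.5 to 0.9 points.

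Coverage at ICC 0.05 / 0.10 / 0.15:

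| Predictor probability by centre | Region intercept | Centre intercept |
|---|---|---|
| 0 or 1 (fully set by centre) | 88.7 / 83.2 / 78.4% | 93.8 / 93.0 / 93.0% |
| 0.1 or 0.9 | 91.0 / 86.8 / 82.4% | 93.9 / 94.2 / 93.6% |
| 0.3 or 0.7 | 93.7 / 92.2 / 92.2% | 94.6 / 94.0 / 94.0% |
| 0.5 everywhere (patient-level) | 95.2 / 93.7 / 94.6% | 95.3 / 94.0 / 95.0% |

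For a predictor set by centre, the region intercept does hardly better than ignoring clustering: 83.2% against 83.3% from the formula at ICC 0.10. In a separate run of the same layout, the interval for the overall mean was only mildly affected, with coverage of 94.8, 93.6 and 93.0% at ICC 0.02, 0.05 and 0.10.

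**The case against.** **The analyses are exploratory.** No formal testing is planned, the main aim is descriptive summary, longitudinal mixed models are only an option, and no decision hangs on this model. This stands and lowers the priority. It does not make the stated grouping right, because readers of an exploratory registry rely on the intervals.

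**The SAP is still to come.** That would answer a missing detail. Here the protocol already fixes the level: an SAP that follows it inherits the problem, and one that uses centre departs from it.

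**Centre appears in the Cox models.** It does, but only for time-to-event outcomes, only if sample sizes allow, and only as an alternative to region. It does nothing for the functional and patient-reported outcomes.

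**Most listed covariates are patient characteristics.** This stands. A reader might infer that all intervals from the region model are too narrow. The documents do not support that: age, gender, smoking, baseline scores and similar covariates vary mostly within centres, where coverage stays near nominal. Among the listed covariates, type of implant is the clearest candidate for centre dependence, and the protocol does not say how strongly it follows the centre.

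**Region as both covariate and grouping level.** Because "Geographic region" is also in the covariate list, a reader might infer that region enters the same model twice and its random variance cannot be identified. The list names potentially important covariates and does not say which model each one enters, so the text does not establish this.

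**Conclusion.** Wrong as written; should-fix. The sentence sets out to address centre effects and specifies a structure without a centre level. That conclusion rests on the text and Table 1 alone and needs no assumed ICC.

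The size of the consequence does depend on assumptions: a centre ICC of 0.05 to 0.15, an even split of patients, and how closely a predictor follows the centre. Under these, coverage of a nominal 95% interval is about 78 to 89% for a predictor fully set by centre, about 82 to 91% when it is 0.1/0.9 by centre, about 92 to 94% when it is 0.3/0.7, and near nominal for patient-level predictors. At an ICC of 0.02 the loss is small even for a predictor fully set by centre (92.6% by the formula). Table 1 lists the sites currently included, so the regional split could change before analysis.

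**What to change.** - Change the sentence so that patients, with their repeated measures, are nested within treating centre as a random intercept.
- Keep region as a descriptive stratum, and state that each non-European region is currently represented by one centre. A combined non-European category is not advisable, since it would pool three unrelated hospitals on three continents.
- In the Cox models, account for centre by clustered robust standard errors or a shared frailty where event numbers permit.

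The cost is a few lines of text and a change of grouping variable in the model. The site is known for every patient, so no new data are needed. Intervals for centre-related predictors become wider, by up to the √DE factors above (1.23 to 1.59 at ICC 0.05 to 0.15), and the claim to compare regions becomes weaker. With 18 centres the simple ± 1.96 SE interval still falls slightly short (about 93 to 95%), so a small-sample degrees-of-freedom correction in the SAP would be sensible.

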#### Treatment details

Surgical details to be documented include:

Side (left, right or bilateral).Date and duration of the surgery (minutes).Use of preoperative virtual surgical planning.Implant type (stock or customised implants, brand).Material (mandibular and fossa components).Screws used (normal or back-up/safety), including side (left/right), number, length and diameter.Details of surgical approach as per AO standards (preauricular, retromandibular, submandibular or facelift).^34^Use of intermaxillary fixation (intraoperative or postoperative).Length of hospitalisation (days).Details of antibiotics and steroids.Details of functional rehabilitation (type and duration).Details of the type and frequency of pain medication (if indicated).

If applicable, additional surgical procedures (eg, dental extractions, orthognathic surgery, coronoidectomy, eminectomy, resection, reconstruction, bone or fat grafting, soft tissue flap, hardware removal) will be recorded. If a contralateral TMJ replacement is performed during the study, surgery details will be collected.

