## Discussion

The number of TMJ replacement surgeries has steadily increased worldwide.^20 21^ In the USA, Onoriobe *et al*^21^ reported a 38% increase in procedures from 2005 to 2014, with demand for TMJ total joint replacement devices projected to grow by another 58% by 2030. Despite this trend, high-quality clinical data are scarce, and treatment indications, surgical methods and outcome assessments vary widely among clinicians and researchers worldwide.

Currently, no comprehensive international database exists to track outcomes or treatment-related AEs, and only one national TMJ registry has been established.^32^ The proposed TMJ registry aims to address this gap as a multicentre, prospective observational study involving international sites. It will document treatments based on current standards of care and collect real-world data across various healthcare settings. This global effort will enable comparisons of treatment practices, outcomes and complication rates, support the identification of best practices and meet the critical need for standardised data collection.

The novelty of the present study protocol lies in its aim to create a large, comprehensive dataset on alloplastic TMJ replacement. Establishing a global database will support research on long-term outcomes and improvements in QoL, ultimately guiding evidence-based decision-making and optimising patient care worldwide.

This study has some limitations. The sample size of approximately 200 patients may limit the ability to detect rare complications or perform adequately powered subgroup analyses. Variability in treatment protocols across participating centres may introduce heterogeneity and residual confounding, which could affect data consistency and comparability. In addition, the use of five PROs could be burdensome for patients, potentially lowering completion rates, and the absence of a TMD-specific QoL questionnaire, such as the Diagnostic Criteria for Temporomandibular Disorders (DC/TMD),^43^ necessitating reliance on instruments adapted from studies of edentulous populations, may limit the sensitivity of outcome assessment. The registry, however, could serve as a platform for the future integration or validation of TMJ-specific PROMs as they become available, without overburdening participants during this exploratory phase.

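### Event-level adverse event rates are fixed per patient only, so rates of side-specific complications rise with the share of bilateral cases at equal risk per joint

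*Protocol article*

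**What the plan says.** The adverse event sentence in the Statistical analysis section reads: "The AEs will be summarised at both patient and event levels, with rates calculated using the total population as the denominator", and continues "regardless of dropouts, with 95% CIs provided". I read the total population as a count of patients. No other denominator for adverse events appears in the article, and the method for the confidence intervals is not named.

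The same article allows more than one replaced joint per patient. Treatment details records "Side (left, right or bilateral" at surgery and adds: "If a contralateral TMJ replacement is performed during the study, surgery details will be collected". The footnote to Table 2 on treatment details likewise provides for a second side operated on later in the study.

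The Adverse events section lists many complications that belong to a side or an implant: "These include fixation failure (implant loosening, breakage or instability), dehiscence of incision, wound infections, neurological-related (facial nerve damage, Frey’s syndrome, sensory disturbances or altered hearing". Heterotopic ossification and disarticulation follow in the same list.

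Three other provisions bear on the point. Unilateral or bilateral replacement is a listed covariate (Covariates). Analyses are to be stratified by clinically relevant categories (Statistical analysis). The clustering described there is of patients within regions, with treating centre as a possible Cox covariate; no level for joints within a patient is mentioned.

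**The concern.** For a complication that can occur once on each operated side, the natural number at risk is replaced joints. Dividing events by patients gives the mean number of events per patient. That is a valid description, but it mixes two things: how risky each joint replacement is, and how many joints each patient had replaced.

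The mixing matters when rates are set beside each other. The Discussion says: "This global effort will enable comparisons of treatment practices, outcomes and complication rates". If centres, regions or implant types differ in how often they operate on both sides, their event-level rates will differ even when every joint carries the same risk. A reader could take that difference for a difference in surgical or device performance. The problem is separate from dropout and would arise with complete follow-up.

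**Working it through.** **Inputs from the article.** One patient denominator for both levels (Statistical analysis); one or two replaced joints per patient (Treatment details, Table 2 footnote); side-specific events on the list (Adverse events). The planned size is 200: "The planned sample size of 200 patients is based on the estimated number of eligible participants expected to be enrolled". The article states no adverse event rate, so there is no figure to reproduce.

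**Assumed inputs.** Risk per joint p = 5% or 10%, the same in unilateral and bilateral patients. Bilateral share b, the fraction of operated patients with two replaced joints, from 0 to 1. Correlation rho between the two joints of one patient of 0, 0.3 or 0.6.

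**Event-level rate on the stated denominator.** N patients have N(1 + b) replaced joints and N(1 + b)p expected events. Dividing by N gives p(1 + b).

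| b | p = 5%: events per 100 patients | p = 10%: events per 100 patients |
|---|---|---|
| 0 | 5.0 | 10.0 |
| 0.25 | 6.25 | 12.5 |
| 0.50 | 7.5 | 15.0 |
| 0.75 | 8.75 | 17.5 |
| 1 | 10.0 | 20.0 |

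Divided by N(1 + b) joints instead, the rate is p in every row.

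**Two groups compared.** Split the 200 patients into two groups of 100, with p = 10% in both.
- 20% bilateral: 120 joints, 12 expected events. Per patient 12/100 = 12%; per joint 12/120 = 10%.
- 60% bilateral: 160 joints, 16 expected events. Per patient 16/100 = 16%; per joint 16/160 = 10%.
- Ratio per patient 16/12 = 1.33; ratio per joint 1.00.

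**Patient-level proportion.** With at most one event of a kind per joint, the share of patients with any event is (1 − b)p + b[1 − ((1 − p)² + rho·p(1 − p))]. At p = 5% and b = 0.5:
- rho = 0: 0.025 + 0.5 × 0.0975 = 7.4%
- rho = 0.3: 0.025 + 0.5 × 0.08325 = 6.7%
- rho = 0.6: 0.025 + 0.5 × 0.069 = 6.0%

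With no bilateral cases it is 5%. The patient-level proportion therefore also rises with b, though less, particularly when the joints are correlated.

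**Precision of a per-joint rate.** At p = 5%, N = 200 and b = 0.5 there are 300 joints. Ignoring pairing, the standard error is √(0.05 × 0.95/300) = 1.26 percentage points. Allowing for pairing, the variance of the event count is N[(1 − b)p(1 − p) + 2b·p(1 − p)(1 + rho)]. At rho = 0.3 this is 200 × (0.02375 + 0.06175) = 17.1, so the standard error is √17.1/300 = 1.38 points. At rho = 0.6 it is 200 × (0.02375 + 0.076) = 19.95, giving 1.49 points. At rho = 0 it stays at 1.26.

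**The case against.** The strongest reply is that events per patient is an accepted safety summary. Nothing in the article labels it a risk per implant, and the proportion of patients affected will be reported beside it. The registry is exploratory with no formal hypothesis testing, its limitations say that the design rules out direct comparison across interventions, and the Discussion acknowledges heterogeneity and residual confounding. Laterality is recorded and listed as a covariate, and stratified analyses are foreseen. Some listed events, such as malocclusion or sensitivity to material, are not clearly tied to one joint. The analysis plan, not shown, could add more.

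Much of this stands, and it keeps the point modest. It does not remove it. The denominator is a choice the article states, not a detail it leaves open. Neither the covariate list nor the stratification sentence is tied to adverse event rates. Stratifying by laterality would remove the case-mix effect, but within bilateral patients events per patient would still be twice the risk per joint. The patient-level proportion does not repair the event-level rate, and it also moves with the bilateral share.

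A reader might go further and infer that the promised 95% confidence intervals ignore pairing and are too narrow. The article does not support that. It names no interval method, a patient denominator does not dictate a variance estimator, and an interval clustered on patient fits the text. Any loss of coverage would depend on an assumed method and an assumed correlation. Nor does the text support reading events per patient as an error in itself.

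**Conclusion.** The concern holds for the denominator and only there. For side-specific and implant-related events, the single patient denominator makes the event-level rate p(1 + b), so groups with more bilateral cases show higher rates at equal risk per joint. In the illustration the inflation is 12% against 16%, a ratio of 1.33, where the per-joint risk is 10% in both groups. This rests on assumed bilateral shares of 20% and 60%, an assumed joint risk, and equal risk per joint in unilateral and bilateral patients. The real size cannot be derived from the article. No conclusion about the width of the plan's confidence intervals is drawn. This is a worthwhile improvement of modest severity.

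**What to change.** Amend the adverse event sentence in the Statistical analysis section, and carry the change into the analysis plan:

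- Keep the proportion of patients with at least one event, and report it also separately for unilateral and bilateral patients.
- For side-specific and implant-related events, add an event-level rate per replaced joint. Count a later contralateral joint from its own operation.
- Give that rate a 95% confidence interval that allows for two joints per patient, for example from generalised estimating equations with robust variance or a bootstrap that resamples patients.
- Keep events per patient for events that are not side-specific.
- Make sure adverse event records identify the operated side. The case report form is not shown and may already do so.

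The cost is a sentence or two, minor programming and possibly side queries for events already entered. Per-joint intervals will be somewhat wider than ones that ignore pairing if the two joints of a patient are positively correlated.
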